**Methods:**

RECONCILE is an ethics approved (20/LO/0366) single centre, prospective, longitudinal, observational cohort study of recently diagnosed (within 12 months), organ-confined Gleason 3 + 4 cancers (MCCL ≤10mm) currently under active surveillance. 60 treatment-naïve participants with a concordant MRI lesion (Likert score 4 or 5) and PSA ≤ 15 ng/ml will be recruited.

Blood, urine and targeted prostate tissue cores will be subject to next generation sequencing at baseline and one year in all participants. Semen will be collected from a specified sub-population. Baseline and interval MR images will be extracted from standard of care prostate MRI ahead of radiomic analysis. Data extracted from radiological and biological samples will be used to derive the association of molecular change and radiological progression, the primary outcome of the study.

To compensate for spatial intratumoral heterogeneity and inherent sampling bias, a molecular index will be derived for each participant using the molecular profile of tumour tissue at both baseline (MolBL) and one year (MolFU). We will extract a ΔMolBL:MolFU score for each participant. Molecular progression will be defined as a MolBL:MolFU score >95% CI of the combined ΔMolBL scores. Radiological progression is defined as a PRECISE score of 4 or 5. The study is powered to detect an association with a statistical power of 80%.

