## 2. Design and methods: The RECONCILE study protocol

### 2.1 Study overview

RECONCILE is a single-centre, prospective, longitudinal, observational cohort study of patients recently diagnosed with localised prostate cancer. The study represents level 1b evidence for prognostic and diagnostic studies [14]. This manuscript is based upon study protocol version 2.0 10July2020.

RECONCILE will recruit 60 evaluable participants with a PSA of ≤ 15ng/ml, organ-confined Gleason 3 + 4 cancer (MCCL ≤ 10mm) and an MR concordant lesion (Likert or Prostate Imaging Reporting and Data System—PI-RADS—4 or 5) who have chosen to pursue active surveillance. Participants must have no history of prior prostate cancer treatment or anti-androgen exposure in the preceding 6 months (including 5-alpha reductase inhibitors) to be eligible for enrolment. Full inclusion and exclusion criteria are outlined in Table 1.

**Table 1 pone.0295994.t001:** RECONCILE study inclusion and exclusion criteria.

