#### 4.4.1 Molecular index

We will use next-generation sequencing and expression analyses to derive a quantitative molecular index for every baseline (MolBL) and follow-up (MolFU) biopsy. For each individual patient, the difference in the baseline molecular index between the two baseline biopsy samples (ΔMolBL) will be calculated. This is a measure of intrinsic patient tumour heterogeneity and will identify molecular features which are consistent between lesions, overcoming sampling bias. The relationship of the targeted biopsy sample to the longitudinal axis of the cancer lesion will also be taken into account using multi-slice processing and separate processing of the sample extremities.

We will use the same metrics to generate a MolFU for each patient using per protocol follow-up biopsy samples. We will then compare MolBL and MolFU for every individual patient and extract a ΔMolBL:MolFU score. Patients will be classified as having a molecular progression event if the ΔMolBL:MolFU score is greater than 95% CI of the combined ΔMolBL scores. Researchers generating the molecular index score will be blinded to radiological progression annotations.

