### 6.5 Prostate tissue collection

Consenting patients will donate three additional cores of prostate tissue at the time of their baseline standard of care prostate biopsy. At exit, participants will donate a further 3 biopsy tissue cores, or five additional cores if there is a new lesion on mpMRI. Cores 4 and 5 will be collected from the highest scoring, greatest volume new lesion.

We do not anticipate that collection of additional tissue cores for research will increase the likelihood of side effects or adverse events relative to standard of care biopsy alone. The risks and adverse outcomes of prostate biopsy quoted within the RECONCILE patient information sheet are outlined in Table 3. Research cores will be targeted using visual-estimation to areas of interest identified on pre-biopsy mpMRI. Research cores will only be attempted after all required standard of care diagnostic biopsies have been collected.

**Table 3 pone.0295994.t003:** Side effect profile of a targeted transperineal prostate biopsy as stated in the RECONCILE study patient information sheet.

Side effect	Proportion of men	Duration
Pain/discomfort in back passage	Almost all	Temporary for 1–2 days
Burning when passing urine	Almost all men	Self-resolving, 1–3 days
Bloody Urine	Almost all	Self-resolving, 1–7 days
Bloody Sperm	Almost all	Lasting up to 3 months
Poor erections	1–2 in 100	Temporary for 1–6 weeks
Infection of skin/urine	1–2 in 100	7 days with treatment with antibiotics
Infection of skin/urine needing admission and intravenous antibiotics	Less than 1 in 500	7–14 days with treatment with antibiotics. Rarely up to 28 days of antibiotics after leaving hospital.
Difficulty passing urine requiring catheter placement for up to a week. A catheter is a soft plastic tube placed into the bladder to drain urine.	1 in 100	3–7 days
Bruising of skin	Almost all	Self-resolving, 7–14 days
Bruising spread to scrotum	1 in 100	Self-resolving, 7–28 days

All cores will be collected in line with the study Tissue Collection SOP. The first and second research cores will be collected from the centre of the lesion with the highest Likert / PIRADS score and greatest volume (lesion 1). Lesion volume will be determined by MRI reporting.

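### Molecular progression is judged against a 95% confidence interval of baseline core-to-core differences, which is not a limit for individual change and, read literally, would label about 18–40% of unchanged patients as progressors

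*Protocol article*

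**What the plan says.** Section 4.4.1 defines the reference quantity within each patient: "the difference in the baseline molecular index between the two baseline biopsy samples (ΔMolBL) will be calculated". It presents this as a measure of the tumour's own heterogeneity. The investigators will then "compare MolBL and MolFU for every individual patient and extract a ΔMolBL:MolFU score", and a patient counts as a molecular progressor if this "score is greater than 95% CI of the combined" ΔMolBL scores. The Methods paragraph of the abstract gives the same rule: "Molecular progression will be defined as a MolBL:MolFU score >95% CI of the combined ΔMolBL scores".

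Both baseline cores come from one lesion. Section 6.5 states: "The first and second research cores will be collected from the centre of the lesion with the highest Likert / PIRADS score and greatest volume". The exit visit samples the lesion in the same way, so there are two lesion cores per visit.

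The resulting M+/M− label is one axis of the contingency table in section 4.3. It also enters the primary outcome in section 7.1, the proportion of concordant molecular and radiological progressors.

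Three other places bear on the cut-off. Section 4.6.1 derives a minimum precision for molecular change from the table populated with radiological results. Section 4.6.2 applies that precision to decide who is a molecular progressor. Section 8 lets the ratio of progressors inform the precision of the interval.

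**The concern.** The question asked of each patient is whether the lesion changed by more than two cores of the same lesion differ at a single visit. That requires a limit drawn from the distribution of individual core-to-core differences. A confidence interval answers another question, namely how precisely a pooled parameter (ordinarily the mean) is known. Its width falls as the cohort grows, although tumours do not become less heterogeneous when more men are recruited. A patient with no molecular change can therefore fall outside it easily, and more easily in a larger study.

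The label feeds the primary outcome directly. An unchanged patient wrongly called M+ adds a spurious concordant pair if he is a radiological progressor. If he is not, the error turns a true concordant negative into a discordant pair. Either way the concordance proportion is distorted, and random M+ calls weaken any real link between molecular and radiological change.

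**Working it through.** **The plan's own figures.** The article gives no false-positive rate for the molecular label, so there is none to reproduce. Its one statistical figure, power of at least 0.8 in section 8, does reproduce. With discordant proportions 0.25 and 0.05 (sum ψ = 0.30, difference d = 0.20) and N = 60, the Miettinen approximation gives Φ[(−1.96 × 0.30 + 0.20 × √(60 × 0.30)) / √(0.30² − 0.20² × 3.30/4)] = Φ(0.2605/0.2387) = 0.86. That arithmetic is not in question here.

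**Inputs from the document.** N = 60 (section 2.1: "RECONCILE will recruit 60 evaluable participants"); two lesion cores per visit (section 6.5); a 95% interval (section 4.4.1).

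**Assumptions.** Core values are normal with equal variance at both visits, no patient truly changes, and the interval is that of the mean. The article does not say whether differences are signed or absolute, or whether single cores or two-core means are compared, so all four combinations are shown.

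**Scale.** Let one core have SD 1. A core-to-core difference then has SD √2, written S. A single-core baseline-to-follow-up difference also has SD S. A difference of two-core means has variance 1/2 + 1/2, hence SD 1 = S/√2.

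**Upper limit of the 95% CI at N = 60, using t(59) = 2.00**
- Signed: the mean is 0, so the limit is 2.00 × S/√60 = 0.258 S.
- Absolute: the mean is 0.798 S and the SD 0.603 S, so the limit is 0.798 S + 2.00 × 0.603 S/√60 = 0.954 S.

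**Unchanged patients above the limit**

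| Reading | Closed form | Simulation (20,000 trials) |
|---|---|---|
| Signed, single core | P(Z > 0.258) = 39.8% | 40.0% |
| Signed, two-core mean | P(Z > 0.258 × √2) = 35.7% | 36.0% |
| Absolute, single core | P(\|Z\| > 0.954) = 34.0% | 34.3% |
| Absolute, two-core mean | P(\|Z\| > 0.954 × √2) = 17.7% | 18.1% |

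If all 60 patients were unchanged, 18–40% would be about 11 to 24 men labelled M+.

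**Dependence on N.** The signed upper limit is 0.33 S at N = 37, 0.26 S at 60, 0.18 S at 120 and 0.09 S at 500. For absolute single-core differences the false label rate rises from 32% to 34%, 36% and 40% at those sizes, with a limit of 42%. For signed scores it tends to 50%.

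**Comparison with a reference limit.** Absolute scores set against the empirical 95th percentile of the 60 baseline differences give 6.3% (single core) and 1.0% (two-core mean). Signed scores against a known upper limit of 1.96 S give 2.5% and 0.3%. Apart from estimation error, these rates do not depend on N.

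**Sensitivity to between-visit variation.** If re-targeting or batch effects add a between-visit SD equal to the core SD, the absolute two-core reading of the CI rule rises from 18% to 34%. The reference-limit rates for absolute scores rise to 12.8% (single core) and 6.5% (two-core mean).

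**The case against.** The strongest reply is that the authors meant a 95% reference interval and used the familiar abbreviation loosely. Section 4.4.1 presents ΔMolBL as a measure of heterogeneity and never says that the interval is for the mean. The purpose fits a reference interval, and on that reading the false label rate is only about 1–6%. This may well be the intention. It does not rescue the wording: the term appears in both statements of the rule, no other section redefines it, and sections 4.6.1 and 8 speak of precision, which is the language of estimation.

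A second reply is that a condensed article may leave the score formula and its sign to the full protocol or SAP. That stands, and the missing formula is not criticised here. The criticism concerns the limit that the article does state.

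Two stronger readings should be resisted. A reader might infer that a third of unchanged patients will certainly be mislabelled. The documents do not support this. The figure depends on the literal reading and on the assumptions above, and one of the four plausible scores gives 18%.

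A reader might also infer that the false M+ calls would make McNemar's test reject spuriously. That does not follow from this defect. With an assumed 20% of radiological progressors (a figure not in the documents) and independent labels, rejection is 58–68% at an M+ rate of 40%, but 61–71% at 5% and 84–90% at 2.5%. A correct limit would therefore not lower it. Those rates arise because McNemar's test compares two marginal proportions, which is a separate matter.

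**Conclusion.** The point holds as a mis-specified limit. As written, the rule compares an individual with an interval for a pooled mean, and so does not do what section 4.4.1 sets out to do. At N = 60, with normal errors, equal variances and no true change, between 18% and 40% of unchanged patients would be called molecular progressors, depending on how the score is built. A 95% reference limit would give about 1–6% where visits add no variation. The direction, and the growth of the error with N, hold for all four scores. The exact percentages rest on assumptions about an index whose scale the article does not give. If a reference interval was intended, the defect is one of terminology, but it still needs correcting because the rule defines a component of the primary outcome. No claim is made about rejection rates of the planned test.

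**What to change.** In section 4.4.1 and the abstract, replace the 95% confidence interval with the 95th percentile, or the upper 95% prediction limit, of the individual baseline differences. Compute it on the same scale as the follow-up score: both signed or both absolute, both single-core or both two-core means. If two-core means are compared, note that under equal variances their difference has SD 1/√2 times that of a core-to-core difference. A limit taken unscaled from core-to-core differences would then be stricter than its nominal 95%.

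Reword sections 4.6.1, 4.6.2 and 8 to match, so that the limit is fixed from the baseline differences alone and is not adjusted using the radiological table or the ratio of progressors. Changing 4.4.1 and the abstract without these sections would leave two competing rules.

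The cost is a few sentences of text and no new data. The consequence to accept is that fewer patients will be classed M+.

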#### 4.4.2 Spatial heterogeneity

Spatial heterogeneity within the same tumour will be taken into consideration. As all biopsies will be taken transperineally and directed to the centre of the lesion in axial plan, a biopsy core explores the longitudinal morphometric axis of the cancer. Using a standard biopsy gun, the length of tissue sampled is 17mm long and 16gauge (1.29mm) thick. Patients under active monitoring are not expected to have cancer involvement of the whole biopsy core length. The maximal cancer core length harboured on a single core and percentage of cancer involvement of a core are well established considerations when entering a surveillance programme. These specimens will reflect the centre, the periphery and the immediately adjacent tissue of the cancer.

The biopsy sample will be analysed as a multi-slice process. The first slice will undergo standard Haematoxylin and Eosin staining. The extremity of the cancer observed within the core will be analysed separately.

### 4.5 Assessment of radiological progression

Radiological progression will be defined using the PRECISE score for which consensus has been published [11]. A PRECISE score of 4 or 5 will define radiological progression, a PRECISE score of 1, 2 or 3 will define radiological regression / stability ie non radiological progressors.

#### 4.5.1 Inter-observer variability

To compensate for inter-observer variability, double reading of MRI will be performed. In case of discordance between radiologists regarding the binary outcome of progression (PRECISE 4 and 5) vs non progression (PRECISE 1, 2 and 3), a third, independent reviewer will determine the final result in disagreement cases. All 3 radiologists will be involved in reporting RECONCILE imaging. A third party, not involved in the radiology assessment, will be unblinded to the radiology report and if necessary, will reallocate indeterminate MRIs for reporting. The 3rd radiologist will be blinded of their 3rd reviewer role.

#### 4.5.2 Blinding from biopsy results

Radiologists reporting the second mpMRI will be kept blinded from the results of the second set of biopsies, performed at 1 year from baseline.

#### 4.5.3 Consensus meeting

A joint consensus meeting with the urologist performing the biopsies, trial radiologist and pathologist will review the consistency of radiological progression and standard of care biopsy results. Sampling effect will be taken into account. Blinding to the results from molecular analysis will be maintained during this process.

#### 4.5.4 Final determination of radiological progressors

The final number of radiological progressors and non-radiological progressors will be established using the double reported MRIs and consensus meeting outcome if needed.

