### 8. Statistical analysis

The primary statistical analysis will be to estimate the association of match‐paired binary responses (molecular and radiological progressors) since the results of the two tests are not independent. For McNemar’s test of paired proportions using the Miettinen normal approximation with a two‐sided significance level of 0.05, a sample size of 60 achieves a power of at least 0.8 when the discordant proportions are 0.05 (5%) and 0.25 (25%) of the total number. The ratio of progressors will inform the precision of the IC for the molecular analysis. Study results will be shared in peer reviewed journal articles.

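### A consensus meeting that sees biopsy results may change final radiological progressor status, against the MRI-only definition and the blinding to the second biopsies, and this can inflate the primary concordance

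*Protocol article*

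**What the plan says.** All references are to the protocol article.

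- **4.5** defines radiological progression as PRECISE 4 or 5 and non-progression as PRECISE 1 to 3. Only imaging enters the definition.
- **4.5.1** provides double reading. When the two readers differ on the binary status, "a third, independent reviewer will determine the final result in disagreement cases".
- **4.5.2** adds that "Radiologists reporting the second mpMRI will be kept blinded from the results of the second set of biopsies", those taken one year after baseline.
- **4.5.3** sets up a joint meeting of the biopsying urologist, a trial radiologist and a pathologist, who "will review the consistency of radiological progression and standard of care biopsy results". Possible sampling effects are to be considered, and the meeting stays blinded to the molecular analysis.
- **4.5.4** states that the final numbers of radiological progressors and non-progressors "will be established using the double reported MRIs and consensus meeting outcome if needed".

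The resulting label fills the table of radiological against molecular status (4.3, 4.6.1) and enters the primary outcome in 7.1, the proportion of concordant pairs. Section 7.2 lists concordance of histological with radiological progression as a secondary outcome.

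**The concern.** Once the third reader has ruled, every scan has a binary status. The only new information the meeting brings is histology and a judgement on biopsy sampling. Letting its outcome enter the final label therefore reopens what 4.5.2 closes, and the label is no longer the MRI-only quantity defined in 4.5.

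The blinding to molecular results does not remove this route. Research cores 1 and 2 come from the centre of the index lesion, in the same session as the standard of care biopsy (6.5), and slices of the standard of care blocks also go to research analysis (6.7). If histological change goes with molecular change in that lesion, moving the MRI label towards histology also moves it towards the molecular label.

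Two estimates are at stake: the concordance and association of molecular with radiological progression, and the histology-radiology concordance. For the second, no correlation assumption is needed; it is enough that the post-consensus label is the one used.

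**Working it through.** **1. The plan's own figure.** Section 8 plans McNemar's "test of paired proportions using the Miettinen normal approximation" at a "two‐sided significance level of 0.05", with N = 60, discordant proportions 0.25 and 0.05, and power of at least 0.8. With ψ = 0.25 + 0.05 = 0.30 and d = 0.25 − 0.05 = 0.20:

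- power = Φ{[d√(Nψ) − 1.96ψ] / √[ψ² − d²(3 + ψ)/4]}
- = Φ{(0.8485 − 0.5880) / √(0.090 − 0.033)} = Φ(1.091) = 0.862

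The stated power holds. The point does not depend on it, and the fix leaves N unchanged.

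**2. The texts side by side.**

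| Question | 4.5 to 4.5.2 | 4.5.3 and 4.5.4 |
|---|---|---|
| What defines the label? | PRECISE on MRI | MRI reads plus meeting outcome where needed |
| Who has the last word? | Third reader | Possibly the meeting |
| Are biopsy results seen? | No | Yes |
| When does the rule apply? | When two readers disagree | Not stated |

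Section 4.5.3 does not say which biopsy is meant. The exit biopsy is the natural reading, because progression is judged on the second MRI.

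**3. Size, under assumed inputs.** None of the following is in the article. Let R be radiological, M molecular and H histological progression.

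- P(R+) = 0.25 and P(M+) = 0.25, with R independent of M and of H, so there is no true association.
- Main case: P(H+) is 0.50 in M+ and 0.15 in M−. Weaker link: 0.40 and 0.20.
- The meeting sets R to H in a fraction f of the cases where they disagree.

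After the meeting, P(R+ | M) = (1 − f) × 0.25 + f × P(H+ | M).
M-R concordance = 0.25 × P(R+ | M+) + 0.75 × [1 − P(R+ | M−)].

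Main case, f = 0.25:
- P(R+ | M+) = 0.1875 + 0.125 = 0.3125
- P(R+ | M−) = 0.1875 + 0.0375 = 0.225
- concordance = 0.25 × 0.3125 + 0.75 × 0.775 = 0.659
- odds ratio = (0.3125/0.6875) / (0.225/0.775) = 1.57

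For histology-radiology concordance in the main case, P(H+) = 0.25 × 0.50 + 0.75 × 0.15 = 0.2375. Disagreement before the meeting is 0.25 × 0.7625 + 0.75 × 0.2375 = 0.369. Concordance after it is 1 − 0.369(1 − f).

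| f | M-R concordance, main | M-R odds ratio, main | M-R concordance, weaker | M-R odds ratio, weaker | H-R concordance, main |
|---|---|---|---|---|---|
| 0 | 62.5% | 1.0 | 62.5% | 1.0 | 63% |
| 0.10 | 63.9% | 1.2 | 63.3% | 1.1 | 67% |
| 0.25 | 65.9% | 1.6 | 64.4% | 1.3 | 72% |
| 0.50 | 69.4% | 2.4 | 66.3% | 1.7 | 82% |

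In the main case the fractions relabel about 3.7, 9.2 and 18.4% of participants (f × 36.9%), or roughly 2, 6 and 11 of 60.

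**4. The planned test.** McNemar's test compares the two margins. In the main case the R+ margin is (1 − f) × 0.25 + f × 0.2375. At f = 0.50 this is 24.4%, against 25% for M+. The discordant cells are then 0.25 × 0.625 = 0.156 and 0.75 × 0.20 = 0.150. Enumerating the test at N = 60 in all these scenarios gives rejection of about 3% (exact version) and about 5% (uncorrected), the same as at f = 0. This holds because the assumed histological progression rate lies close to the R+ rate; a very different rate would move the margin.

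Power is a separate matter. From the plan's discordant proportions, if 10, 20 or 30% of both discordant cells became concordant, concordance would go from 70% to 73, 76 or 79%, and power by the formula in step 1 from 0.86 to 0.82, 0.76 or 0.69.

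**The case against.** The case against has five parts.

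1. **The text permits relabelling; it does not prescribe it.** The meeting reviews consistency, its outcome counts only where needed, and sampling effects are considered, so a discordant biopsy may be discounted. This stands. It rules out treating full deference to histology as the expected case, and it makes small values of f credible.
2. **Direct leakage is closed.** Molecular analysts are blinded to radiological status (4.4.1, 4.6) and the meeting to molecular results. This stands, but only for the direct route.
3. **The histology-molecular link is not documented.** The index uses dedicated research cores, and molecular progression is a change beyond baseline within-patient heterogeneity, not a grade. This stands. The correlation is plausible, but its size is unknown.
4. **The article condenses protocol version 2.0** (2.1), where a trigger or a prior lock may be set out. This lowers confidence. It does not reconcile the rules that the article itself states.
5. **A reader might infer that the meeting raises the false-positive rate of the primary test.** Fisher's test applied to the main-case tables at n = 60 rejects about 8% of the time at f = 0.25 and 23% at f = 0.50. Section 8 plans McNemar's test, not Fisher's, and its rejection rate stays near its usual level in the same tables. The documents do not support that inference.

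**Conclusion.** The conflict between 4.5 to 4.5.2 and 4.5.3 to 4.5.4 is on the page. A status defined on MRI alone and read blind to the second biopsies can be changed by a meeting that sees biopsy results, with no stated trigger or limit.

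If relabelling tends towards histology, and histology is positively correlated with molecular change, the primary concordance is biased upwards. In the illustration the shift is 1.4 to 6.9 percentage points in the main case and about 0.8 to 3.8 with the weaker link, for 10 to 50% alignment. Histology-radiology concordance rises by about 4 to 18 points in the main case, provided that it uses the post-consensus label, which the article does not say. All inputs are assumed, so these figures show direction and order of size and are not forecasts.

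Two stronger readings go too far. A reader might infer that the meeting manufactures the molecular-radiological association; the documents show only an open route to bias. A reader might also infer that histology-radiology concordance becomes true by construction; that needs every disagreement to be aligned, and short of that it is inflated, not determined. The harm is to the concordance and association estimates, not to the type I error of the planned test. Confidence is moderate.

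**What to change.** Amend 4.5.4 so that radiological status, for the primary outcome and for histology-radiology concordance, is the blinded PRECISE classification: two readers plus third-reader adjudication, locked in the database before the consensus meeting. Record the meeting's conclusion as a separate variable, used only in a sensitivity analysis, and report how many labels it would have changed and in which direction.

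The cost is a wording change and one database field, with no extra reads and no change in sample size. The drawback is that some labels judged implausible at consensus stay in the primary analysis; the sensitivity analysis shows how much they matter. Section 4.8 reports only 5 participants through active follow-up, so at that point most labels could still be locked this way.
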